### Behavioural activation intervention

The behavioural activation intervention was adapted from the Revised Behavioural Activation Treatment for Depression manual [33]. Detail about the development of the program through piloting and the adaptions made from the original manual have been provided elsewhere [34]. The primary change to the program was the refocus of content toward improving wellbeing and sense of purpose through meaningful activity engagement, as opposed to a focus on alleviating feelings of depression and low mood. Participants will be provided with a treatment manual to help guide their progress. Based on participant feedback from the pilot study, some minor changes were made to the manual, specifically some content and repetition was removed for brevity, and some language was updated to improve readability.

A breakdown of the six sessions of this intervention outlined in the participant treatment manual are provided in Table 2. Briefly, during the first session participants will be introduced to the concept of wellbeing, the behavioural activation approach, and the activity monitoring. During the second session they will be guided through values identification, and brainstorming activities consistent with their values. They also review their activity monitoring charts and continue with monitoring in the following week. During the third session, participants will begin to select and rank activities according to difficulty and feasibility. They are also encouraged to schedule some of these activities into their monitoring sheets. At the fourth session, participants will review their activities over the previous week, troubleshoot potential barriers and consider seeking support from others, if required. The fifth session consists of a review of values and activities and troubleshooting barriers. The final session will review progress made, and how to apply these skills in the future.

**Table 2 Tab2:** Overview of behavioural activation intervention

Week	Content	Estimated duration
1. Wellbeing	What is wellbeing? The activation approach to wellbeing Stressful events and loss Learning your patterns of behaviour: Introduction to daily monitoring	60 min
2. Life areas, values, and activities	Review of monitoring Troubleshooting problems with monitoring Life areas, values, and activities	60 min
3. Activity selection and ranking	Review of monitoring Review of life areas, values, and activities inventory Activity selection and ranking Daily monitoring and activity planning	60 min
4. Reviewing achievements and seeking support from others	Review of monitoring / activities Troubleshooting problems with activities Seeking support from others Daily monitoring with activity planning	45 min
5. Reviewing achievements and modifying activities	Review of monitoring / activities Troubleshooting problems with activities Review of life areas, values, and activities Review of activity selection and ranking Daily monitoring with activity planning	15–30 min
6. Beyond the program	Review of monitoring / activities Troubleshooting problems with activities Daily monitoring with activity planning Review of progress Preparing for the future	15–30 min

### Active control (multi-component positive psychology intervention)

Inclusion of an active control condition that is comparable to the intervention in terms of the required time, effort, attention and amount of content means that any differences in outcomes between the groups can be attributed to the intervention content, as opposed to non-specific treatment effects [35]. An active control condition may also be more ethical than other forms of control condition as all participants will receive a meaningful intervention upon enrolment into the study [36, 37]. Lastly, as both the treatment and control conditions provide a meaningful wellbeing intervention, participants will be blinded to their allocation to the intervention or control condition, thereby reducing expectation confounds. For the active control in the current study a MCPPI was designed. Positive psychology is a therapeutic approach that aims to improve wellbeing and promote flourishing, as opposed to treating mental illness [38]. MCPPIs, which typically incorporate multiple short positive psychology interventions that aim to generate specific positive emotions, have been found to be effective in increasing wellbeing, especially compared to other therapeutic approaches [23].

The specific concepts and activities included within this intervention were selected according to: (a) their comparative effectiveness based on recent meta-analytic findings [39], (b) their emphasis on cognitive experiences and evaluations, as opposed to behaviour and activity, to minimise content overlap with the BA condition, and; (c) provide a variety of activities to increase the chance that participants will find at least one intervention that appeals to them, or that they find helpful [40]. Original sources for the activities that were incorporated can be found in Table 3. Activities listed in Table 3 without citations were developed or modified for the active control condition.

**Table 3 Tab3:** Overview of multi-component positive psychology active control intervention

Week	Content	Estimated duration
1.Wellbeing, positive emotion and positive psychology	What is wellbeing? Introduction to positive psychology The benefits of positive emotion Reflection	60 min
2. Gratitude and optimism	Review of previous week Gratitude Activities to increase gratitude 3 Good things^1^ Expressing gratitude^2^ Optimism Optimism reflection	60 min
3. Character strengths and forgiveness	Review of week and activities Character strengths and identification Character strength task^3^ Forgiveness Forgiveness reflection	45 min
4. Savouring	Review of week and activities Introduction to savouring Savouring the past activity^4^ Savouring the present activity^5^ Savouring the future activity	45 min
5. Reviewing achievements, troubleshooting and modifying activities	Review of week and activities Troubleshooting problems with activities	15–20 min
6. Beyond the program	Review and reflection of activities Review of progress Preparing for the future	15–30 min

A summary of the six sessions contained in the MCPPI participant treatment manual is provided in Table 3. In the first session, participants will be introduced to the concept of wellbeing, positive psychology and the role of positive emotions. In Sessions 2 through 4, participants will be introduced to one or more types of positive emotions and how those emotions may be of benefit. Participants will then be then provided with a reflection exercise or an activity to help cultivate that emotion. In session five, participants will be encouraged to reflect on the activities learned and troubleshoot and modify activities as required. In the sixth session participants will review the progress made and consider how to apply these skills going forward. Due to resource constraints, participants in either condition will not be offered the opportunity to participate in the alternative condition.

### Assessment

Study outcomes will be assessed via surveys, completed online, or in paper-and-pencil format, depending on participants’ preferences. Initial efficacy of the behavioural activation intervention will be assessed at the 1-week post-program assessment. Data from the 3-month follow-up assessment will be used to examine longer-term durability of effects beyond the 1-week follow-up. Measures are detailed below.

#### Primary outcome measure

The Life Engagement Test (LET; [41]) is a self-report questionnaire measure that will be used to assess the extent to which a person perceives that the activities they engage in are personally valued and meaningful. This scale consists of six items (e.g., “I value my activities a lot”), rated on a 5-point Likert scale (1 = *strongly disagree*, to 5 = *strongly agree*). The LET is scored in two steps. First, items 1, 3, and 5 are reverse coded. Second, the six items are summed such that higher scores indicate a stronger perception that one’s activities are valued. The total scale score will be used. The LET has been demonstrated to have good internal consistency (average α = 0.80) and convergent and discriminant predictive validity [41].

#### Secondary outcome measures

Social engagement will be measured via a series of questions on network size, relationship quality, and contact frequency that were used within the English Longitudinal Study of Ageing [42], and the Health and Retirement Study [43]. The questions are provided three times, with reference to children, other immediate family and friends, respectively. Network size is assessed by two questions that assess the number of (children/immediate family/friends) with whom participants have contact, and a close relationship. Six questions explore both positive and negative qualities of these relationships (e.g., “How much do they really understand the way you feel about things?”) and answers are rated on a 4-point scale (1 = *a lot* to 4 = *not at all*). Contact frequency with children/immediate family/friends was assessed by three questions where participants indicate how frequently they (a) meet up, (b) speak on the phone, and (c) write or email.

Loneliness will be measured using the UCLA Loneliness Scale 10-item version (ULS-10; [44]) will be used to measure the subjective experience of loneliness. This scale consists of 10 items (e.g., “How often do you feel that no one really knows you well?”), which are rated on a 4-point scale (1 = *Never*, 2 = *Rarely*, 3 = *Sometimes*, 4 = *Always*). The 10-item short version of this measure shows good internal consistency (α = 0.89; [44]).

Subjective and psychological wellbeing will be assessed using a number of measures. Affect will be measured using the Scale of Positive and Negative Experience (SPANE; [45]), which includes six items that measure positive feelings (e.g., “pleasant”, “contented”) and six items that measure negative feelings (e.g. “sad”, “angry”). Participants rate how frequently they experienced each feeling over the past 4 weeks using a 5-point scale (1 = *very rarely or never* to 5 = *very often or always*). The scale is reported to have good internal consistency (α = 0.81 to 0.89; [45]) and convergent validity [46]. The Satisfaction with Life Scale [47] comprises five items (e.g., “I am satisfied with my life”) scored using a 7-point scale (1 = *strongly disagree* to *strongly agree*). Higher scores indicate greater life satisfaction (Diener et al. 1985). The scale has been demonstrated to have good internal consistency (α = 0.84; Steger et al., 2006) and correlates positively with optimism and self-esteem (Steger et al., 2006). The Flourishing Scale [45] includes five items (e.g., “I am a good person and live a good life”) and is scored using a 7-point scale (1 = *strongly disagree* to 7 = *strongly agree*). Higher scores indicate greater wellbeing. This scale has good internal consistency (α = 0.84) and convergence with other wellbeing scales [45]. The Self-Compassion Scale Short Form [48] is a 12-item measure that will be used to assess levels of trait self-compassion. Participants indicate how often they act in accordance with a series of statements (e.g., “When something painful happens I try to take a balanced view of the situation”) on a 5-point scale (1 = *almost never* to 5 = *almost always*). This scale has good internal consistency (α ≥ 0.86) and a near-perfect correlation with the long form self-compassion scale (*r* ≥ .97 all samples [48].

Physical health will be assessed via the Medical Outcomes Study Physical Functioning Subscale [49], which is a 10-item measure of physical activity limitations. Participants indicate whether their health limits them in various activities (e.g., “Lifting or carrying groceries”) and if so, the severity of each limitation on a 3-point scale (1 = *yes, limited a lot* to 3 = *no, not limited at all*). The scale has been demonstrated to have strong construct and discriminant validity [50]. A single item measure taken from the Medical Outcomes Study Bodily Pain Subscale was also used to measure pain. Participants indicate “How much bodily pain have you had in the last four weeks” on a 6-point scale (1 = *none* to 6 = *very severe*) [50]. Self-rated health was measured by a one-item measure “how would you rate your overall health at the present time”. Responses are rated on a 5-point scale (1 = *Poor* to 5 = *Excellent*).

Mental health will be assessed using the Hospital Anxiety and Depression Scale [51], which includes two 7-item subscales that measure symptoms of depression and anxiety (e.g., “I feel tense or wound up”). This scale has good internal consistency (α ≥ 0.75 [52]) and convergent validity [53], and is widely used among older adult due to its low reliance on physiological symptoms in the assessment of anxiety and depression [52].

Self-regulation will be assessed by the Goal Adjustment Scale [29], a 10-item measure developed to assess reaction to life goal adjustments. Four items measure participants’ goal disengagement capacities (e.g., “It’s easy for me to reduce my effort towards the goal”), and six items measured their goal reengagement capacities (e.g., “I start working on other new goals”). Reponses are measured on 5-point Likert-type scales (1 = *strongly disagree* to 5 = *strongly agree*). The disengagement and reengagement subscales have adequate (α = 0.75) and excellent (α = 0.91) internal consistency respectively [54].

#### Mechanisms

Possible mechanisms will be further assessed via the Behavioural Activation Depression Scale—Short Form (BADS-SF), and the Engaged Living Scale-Short Form (ELS-SF). The BADS-SF [55] is a 9-item self-report scale that measures activation (i.e., goal oriented, values-consistent behaviour) and avoidance over the past week. Items are rated on a 7-point scale (0 = *not at all* to 6 = *completely*), and higher scores represent greater activation. The BADS-SF has good internal consistency (α = 0.82) and construct validity [55]. The ELS-SF [56] is a 9-item measure that assesses participation in valued activities. It comprises two subscales: “Valued Living” and “Life Fulfilment”. Participants indicate their level of agreement to a series of statements (e.g., “I make choices based on my values, even if it is stressful”) on a 5-point scale (1 = *completely disagree* to 5 = *completely agree*). This scale is reported to have good internal consistency for the total scale (α = 0.88) and subscales (Valued Living α = 0.76; Life Fulfilment α = 0.89) and has demonstrated both convergent and discriminant validity [56].

#### Other measures

At baseline, a brief demographic survey will also be used to assess sex, age, ethnicity, education, current employment status and disposable income. Participants will also be asked questions about housing tenure, and cigarette and alcohol consumption. At week five of the intervention, participants will also complete the MOCA-Blind [57], which is a cognitive screener that can be administered over the telephone. Lastly, a 19-item client satisfaction questionnaire will be administered at the first post-program assessment. The items, adapted from the form used by Mazzucchelli, Rees, and Kane [58], assess participant satisfaction, and perceived usefulness of program intervention. These items are rated on a 7-point scale (1 = *no, definitely not* to 7 = *yes, definitely*), with the final question inviting narrative feedback.

#### Daily questionnaire assessment

State self-compassion will be measured using the six item State Self-Compassion Scale—Short Form [59]. Participants indicate their agreement on a 4-point scale (1 = *not at all* to 5 = *to a great extent*) with statements that reflect the tendency to respond self-compassionately (e.g., “I’m giving myself the caring and tenderness I need”). This scale is highly correlated with the long form of the questionnaire, which demonstrated adequate internal consistency (α = 0.72 to 0.82; [59])

Daily affect will be assessed using a measure of positive and negative affect adapted from Hülür et al. [60]. This 8-item scale contains four items that measure positive feelings (e.g., “relaxed”, “interested”) and four that measure negative feelings (e.g., “lonely”, “irritable”). Participants rate how much they experienced each feeling that day using a 5-point scale (0 = *no experience of the affect* to 5 = *very intense experience of the affect*). The scale has been reported to have acceptable internal consistency for both the positive affect subscale (α = 0.78) and the negative affect subscale (α = 0.67;[60]).

Exposure to stressful events will be measured using a short form of the Daily Inventory of Stressful Events [61]. This questionnaire consists of five questions (e.g., “Did anything stressful happen to you with regard to your personal health?”) to which participants respond “yes” or “no”.

Eudaimonic wellbeing will be measured using two short subscales of Meaning in Life, “presence” and “search” as used in Nezlek, Newman, and Thrash [62]. The Presence subscale consisted of two items: “How meaningful did you feel your life was today” and “How much did you feel your life had purpose today?” The search subscale consisted of two items: “How much were you searching for meaning in your life today?” and “How much were you looking to find your life’s purpose today?”

### Study timeline

Older adults who are on a pre-existing list maintained by the Adult Development Lab will be initially contacted by telephone by a research assistant. They will be provided with details of the study, and if they indicate they are interested in participating, they will be administered the LET over the phone to assess their eligibility to participate. Participants who are recruited by online advertisements will be invited to follow a link where they will be provided some information about the study and invited to complete the LET online to determine eligibility. Participants undertaking the full 6-item LET at telephone screening will be eligible to participate if they score at or below 25. Participants undertaking the online screening will be administered a 5-item version of the LET and will be eligible if they score at or below 21 (the mean of the 5-item scale in a community sample of older adults assessed as part of the broader project, N = 431). The final LET item “I have lots of reasons for living” will be excluded for online participants to reduce the possibility of negative feelings among some participants, given that the item would not appear within the context of either a larger survey, or with the presence of the telephone interviewer as an immediate source of support and/or information. The decision to exclude the final item from the online screener was also based on previous data indicating strong item-specific ceiling effects (M = 4.43 (SD = 0.86) on a scale of 1 to 5; [32]) suggesting limited discriminatory value. All eligible participants will be sent, by post or email, the study information sheet, consent form and baseline questionnaire (marked with a unique 3-digit identifier) to complete and return. Those who elect to receive the baseline by email will be sent a link to the baseline questionnaire hosted on the Qualtrics Online Survey Platform. Once the baseline questionnaire is completed participants are considered fully recruited into the study. Using simple randomisation via Microsoft Excel, participants are then allocated to treatment condition. Randomly allocated to treatment condition, sent the corresponding intervention manual and allocated to a study facilitator. The facilitator will contact the participant by telephone to set up a time for the first session and will be responsible for all contact from that participant from then on.

Participants will then undergo six weekly sessions conducted either via the telephone or via online video conferencing software. A graphical representation of the study timeline is provided in Fig. 1. Between each session they will be provided with some activities to complete. For those in the BA group, the between session activities will be flagged as particularly important to complete. If they are not completed during the week, they will be completed with the facilitator during the next session, as per BA protocol [22]. The MCPPI group will be encouraged to complete the between session activities. Facilitators will track their progress on running sheets which will be used to guide content delivery, document participant adherence and make note of anything relevant that may impact delivery or progress. For two weeks during the fourth and fifth weeks of the intervention, participants will be asked to complete a daily questionnaire, which will be posted to them with a reply-paid envelope to return once completed. It is anticipated these questionnaires will take less than 5 min per day to complete. At the end of the fifth session, participants will undergo the MOCA-Blind [57]. Once they have completed the intervention, participants will be posted or emailed two follow-up questionnaires; the first at one week post intervention, and second at three months post intervention. It is anticipated these will take approximately 30 min each to complete. Once their first follow-up assessment is returned, participants will be sent $100 (AUD) reimbursement for their time in the form of a pre-loaded EFTPOS card.

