### Participants

Older adults aged 65 + from the general population, who have a purpose in life (Life Engagement Test) score at or below the population mean in previous community samples [32] will be eligible to participate. Those with substantial hearing loss, difficulty with English or advanced cognitive impairment (or any other difficulties that meant they could not feasibly take part in a telephone-based intervention, as determined by either the recruiter, or the facilitator at first contact) would not be eligible to participate. Potential participants will be initially identified utilising a list of older adults who have agreed to be contacted for future research participation, maintained by the Adult Development Lab at Flinders University, Adelaide, South Australia as well as through advertisements in Weekend Plus, a digital magazine for older adults produced by the South Australian Government, and email invitations sent to online networks such as the South Australian Office for Ageing Well Feedback Network (a group of older adults who have indicated a willingness to be contacted about research projects or government initiatives). Participants will either be contacted by telephone (e.g., those on our database) or will complete an online screening survey to determine eligibility. To date, all participants recruited have resided within South Australia in either metropolitan, regional and rural areas. Future participants may also be recruited through industry partner organisations such as ECH Inc.

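### Allocation is by Excel with no stated lock, log or independent custody, and the facilitator may apply an open-ended exclusion after the arm has been assigned

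*Protocol article*

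**What the plan says.** Study timeline in the protocol article sets out this order:

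- Baseline comes first: "Once the baseline questionnaire is completed participants are considered fully recruited into the study".
- Allocation follows: "Using simple randomisation via Microsoft Excel, participants are then allocated to treatment condition".
- The participant is then "sent the corresponding intervention manual and allocated to a study facilitator".
- Only after that: "The facilitator will contact the participant by telephone to set up a time for the first session".

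Participants lists hearing loss, difficulty with English and advanced cognitive impairment as exclusions, and adds a catch-all: "or any other difficulties that meant they could not feasibly take part in a telephone-based intervention". The decision is made "as determined by either the recruiter, or the facilitator at first contact".

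The article does not say who runs the Excel draw, whether a list is prepared in advance or each draw is made on the spot, or who can see the result. The section on the active control claims blinding for participants only. Table 1 marks allocation under Pre-program, a column that precedes Baseline.

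**The concern.** Two things combine. First, a spreadsheet does not by itself hide a prepared list, prevent a second draw or record when a draw was made. Those protections come from custody and logging, and none is described. Second, one of the two people entitled to exclude makes that judgement after the arm is fixed, and will deliver that arm.

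The second is the more serious, because it remains even if the draw is perfectly concealed. The catch-all criterion rests on judgement. Facilitators are trained in both conditions, the study hypothesis favours behavioural activation (BA), and the primary outcome is self-reported. If people who sound unlikely to engage are judged unfeasible more readily in one arm than in the other, the groups that remain are no longer those formed by randomisation. Without a record of when each decision was made and what was known at the time, the team could not later show that this did not happen.

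**Working it through.** **1. Order of steps.**

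| Step | Source | Arm already assigned? |
|---|---|---|
| LET screen, by telephone or online | Study timeline | No |
| Feasibility exclusion by recruiter | Participants | No, on the natural reading |
| Consent form and baseline questionnaire returned | Study timeline | No (Table 1 suggests otherwise) |
| Excel allocation | Study timeline | Assigned here |
| Arm-specific manual sent, facilitator assigned | Study timeline | Yes |
| Facilitator's first call, with power to exclude | Participants and Study timeline | Yes |

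No earlier facilitator contact is described. For people recruited online, the article describes a web screen and a posted or emailed baseline form, with no conversation before allocation. On my reading, the facilitator's call may be the first time anyone hears such a participant, so exclusion at that point is a foreseeable event.

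**2. Table 1 against the text.** Table 1 puts allocation before Baseline and Study timeline puts it after. Having baseline complete before allocation is the one protective feature the text does give, so the two places need to agree.

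**3. The plan's own figure.** Inputs from Sample size and analysis: d = 0.52, alpha 0.05, power 0.8, a difference of about 2 LET units. The two-sided normal approximation gives 59 per group. The t-based calculation gives 59.03, which rounds up to the stated 60. Power at 60 per group is 0.806. The figure reproduces, and nothing here changes it. The implied SD is 2/0.52 = 3.85 LET units.

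**4. Simple randomisation is not the fault.** With 120 participants, the 95% binomial range for one arm is 49 to 71, and a 70/50 split leaves power at about 0.795. There are no blocks, so past assignments do not reveal the next.

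**5. Illustration of arm-aware exclusion (assumed inputs).** Suppose a fraction f with the poorest apparent prognosis is excluded in one arm only, and the judgement correlates r with the follow-up LET. The shift in the group difference is

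r × φ(z_f)/(1 − f) × 3.85,

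where z_f is the f quantile of the standard normal and φ its density.

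| f | φ(z_f)/(1 − f) | Shift at r = 0.3 (LET units) | Shift at r = 0.5 (LET units) |
|---|---|---|---|
| 2% | 0.049 | 0.06 | 0.10 |
| 5% | 0.109 | 0.13 | 0.21 |
| 10% | 0.195 | 0.22 | 0.37 |

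Against the target of 2 units, this runs from 0.06/2 = 3% to 0.37/2 = about 19%. These are shifts before baseline adjustment. The document gives neither f nor r.

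**6. Illustration of an unlogged redraw (assumed).** If one unrecorded repeat were possible for a given participant, the chance of a preferred arm would rise from 0.50 to 1 − 0.5² = 0.75. Nothing in the document says that this occurs.

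**The case against.** The strongest reply is that a journal article condenses a fuller protocol, and that custody of the sequence is a detail commonly left there. Excel is only a tool for generating a sequence, and a list produced in it and held by an independent person is properly concealed. This stands. A reader might infer that the study team makes the draw, that staff can see or repeat it, or that the same people draw and exclude. The article says none of these things, and its silence does not establish them. On custody alone, the fair request is to state the arrangement.

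A second reply is that the mixed model adjusts for baseline differences, and Sample size and analysis says so. This also stands in part: selection acting through baseline LET would be largely adjusted for. What remains is prognosis noticed in conversation that the baseline score does not capture. Likelihood-based handling of missing follow-up does not remove that either, because exclusion would then depend on something outside the model.

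A third reply is that no rate of exclusion or redraw is documented. That is correct, so the illustrations are not evidence that bias is present.

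None of these replies reaches the order of steps. That order is read from what the article states.

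**Conclusion.** The point holds in this form: the stated allocation method has no described lock, log or independent custody, and the plan as written permits exclusion by a facilitator after allocation on an open-ended criterion. The second part is documented. It rests on reading the facilitator's first contact in Participants as the scheduling call in Study timeline, the only first contact described. That the facilitator knows the arm by then is an inference from the same sequence.

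The size is not estimable from the document. It is zero if exclusions do not depend on arm, and under the assumptions shown it is a few per cent to about a fifth of the planned difference before adjustment. The documents do not support a claim that the allocation was in fact visible, redrawn or steered. The change is worth making because it is cheap and recruitment was still under way when the article was written.

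**What to change.** For all remaining participants:

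1. Complete and log every eligibility and feasibility decision before allocation, and remove the facilitator's power to declare someone ineligible after it. For online recruits this probably needs a short call by the recruiter first.
2. Release each assignment once, irreversibly and time-stamped, after both baseline and the eligibility decision are logged. This can run through the survey platform already in use ("baseline questionnaire hosted on the Qualtrics Online Survey Platform") or from a list held by someone with no role in recruitment or delivery. Log paper returns by date of receipt and process them in that order.
3. Keep everyone randomised in the analysis, seek their follow-up, and report any later exclusions by arm with reasons. For those already randomised, report facilitator exclusions by arm.
4. Correct Table 1 or Study timeline so that both place allocation at the same point relative to baseline.

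If the Excel list is already held independently, one sentence saying so settles custody; items 1, 3 and 4 still apply. The cost is one logging step per participant, a brief call where no one has yet spoken to the person, and a mid-trial change of procedure that must be dated and reported.
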